#### B) Secondary outcomes

The following secondary outcomes will be examined:Procedures time (minutes)The presence of bleeding during the mesentery sutureHospital stay (days)Occurrence of postoperative small bowel obstruction within 30 days after surgeryShort-term complications within 30 days after surgeryOccurrence of Petersen’s hernia in relation to the use of anti-adhesive agents and anastomosis methodsCondition of the bowel (i.e., strangulation, perforation) at the time of emergency surgery for the treatment of Petersen’s hernias after primary surgery

### Data collection

Although all patients will be followed for 5 years postoperatively according to the cancer surveillance protocol, the primary endpoint is set to the results within 3 years after gastrectomy. Once the last participant reaches the 3-year follow-up observation, we will perform the final single analysis.

All data are recorded and managed accurately according to the appropriate format in the electronic case report form (eVelos system). The central research center evaluates the completeness and accuracy of the data collected and submitted at each center. Although the data collectors are not blinded, they do not influence patient enrollment or the intervention. The data collected are as follows:

#### A) Clinical observations

Preoperative patient’s demographics and physical status: Age, sex, underlying disease, body mass index, ECOG score history of abdominal surgery, and clinical stage of gastric cancerOperative outcomes: Method of gastric resection, extent of lymph node dissection, reconstruction method, total operation time, CLOSURE or MEFIX procedure time, the presence of bleeding during the mesentery suture, and use of anti-adhesion agents during surgeryReoperation outcomes due to internal hernia: Type of herniation (Petersen’s or internal hernia), approach method (laparoscopic or open), condition of the bowel (i.e., strangulation, perforation), and site of herniated small bowel (E-loop or A-loop)Clinicopathologic and postoperative outcome: Pathologic TNM stage, first flatus time, time to start oral feeding, hospital stay, postoperative morbidity, and mortality.

#### B) Detailed complications that occur during the postoperative hospitalization period

Short-term complications are defined within 30 days after surgery and are classified and recorded according to the Clavien–Dindo classification.Post-discharge investigations and long-term complications are as follows:Long-term complications are defined as those occurring 90 days postoperatively.Outpatient follow-up: Occurrence of Petersen’s hernia, other long-term complications, and incidence of readmissionOccurrence of Petersen’s hernia: Petersen’s hernia requires reoperation.

The pathologic Petersen’s hernia is confirmed by surgical findings (i.e., the preoperative hernia is suspected, but hernias in other areas are diagnosed as internal hernias, not Petersen’s hernia). The clinical Petersen’s hernia before surgery is diagnosed through radiologic findings (mesenteric whirling sign, narrowing of superior mesenteric vein and dilated duodenum, etc.) with related symptoms such as nausea or vomiting. Abdominal CT is usually recommended for radiographic examinations. Ultrasonography is possible, but superior mesenteric vessel rotation must be confirmed.

### Data monitoring, auditing, and interim analysis

Researchers and CRC carry out the study at each institution. The entire research process is monitored by the Research Steering Committee, which is composed of the principal investigator (PI) and participating researchers with extensive research experience. Additionally, the Research Safety Monitoring Committee, independent from the study, was established to evaluate the safety of the research.

This study is conducted with respect for the rights and welfare of patients, and it is monitored whether the reported data related to the clinical research were accurate, complete, and verifiable compared with the evidence documents and whether the clinical research is conducted in accordance with the approved plans and relevant regulations. The patients’ original records, medical records, and data repositories (i.e., research files) will be reviewed every 6 months. All personal data will be stored in password-protected program; only authorized coordinator can access. The progress of clinical trial will be also reviewed, and any violations or noncompliance will be reported according to the institutional bioethics committee reporting procedure.

For reasons of safety and efficiency, interim analyses are planned to be conducted once 33% (first interim analysis) and 66% (second interim analysis) of the sample size have been recruited, and their results are available. The O'Brien-Fleming stopping rule will be applied to ensure efficacy and safety. If the primary outcome for the MEFIX group is superior to that of the CLOSURE group, with a *p*-value of less than 0.0005 at the first interim analysis, or less than 0.014 at the second interim analysis, consideration will be given to early termination of the study. This will allow for a prompt evaluation of the MEFIX method’s efficacy. In the final (third) analysis, we will not adjust the *p*-value to evaluate primary and secondary endpoints. There is no predefined stopping rule for safety related to complications. Any significant potential harm or serious adverse events (AEs) related to the procedures are considered grounds for stopping the trial.

This study is a prospective, multi-institutional clinical study. The steering committee will convene every 6 months to evaluate the progress and safety of the trial. Any safety concerns will be reported to the Research Safety Monitoring Committee, an independent organization from this trial, and assessed in the following cases.The case of surgery due to Petersen’s hernia, which is the primary endpoint of this study, does not fall under the safety evaluation. During the interim analysis, if the upper margin of 9.7% of the incidence of Petersen’s hernia known through the existing references is exceeded, the research safety monitoring committee evaluates the safety of the study.During the interim analysis, an evaluation will be conducted if there is a significant increase in complications suspected to be strongly related to the surgical method being performed in the experimental group.

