### Sample size

Sample size calculation was based on an assumed proportion of Petersen’s hernia of approximately 1.15% for the conventional close method from our previously published papers [11]. The estimated difference in Petersen’s hernia proportions between close and MEFIX methods was assumed as 0.0% based on the previous similar study [11]. Thus, we set the inferiority threshold at 3% for clinical relevance. Therefore, if the proportion of Petersen’s hernia of the MEFIX method is less than 4.15%, the MEFIX method is not considered inferior to the conventional close method.

A sample size of 199 per arm is required for a proportion test with a one-sided significance level of 0.025 and power of 80% with no difference of hernia proportion between the two methods and a non-inferiority margin for the MEFIX method of 3% (non-inferiority limit = 0.03, treatment A (experimental) group = 0.0115, treatment B (control) group = 0.0115). Further, we decided to increase the sample size by 10% to cover possible dropouts. Consequently, 222 participants were included per group, and a total of 444 were needed. This calculation was performed as the PASS 13 (Power Analysis and Sample Size Software (2014). NCSS, LLC. Kaysville, UT, USA).

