### Adverse event

An adverse event (AE) refers to any undesirable medical occurrence in a patient that does not have a causal relation with the treatment. Therefore, an abnormal reaction is an unexpected and undesired symptom (for instance, abnormal laboratory test results) or a transient illness occurring independently of the surgery and without obvious causality. The severity of the AEs is assessed using the National Cancer Institute’s Common Terminology Criteria for Adverse Events (NCI-CTCAE), version 4.03, with detailed information being recorded in the patient’s medical record.

Serious AE is defined as a critical anomaly response if as follows: All deaths within 30 days of surgery are reported as significant AEs, regardless of the causality of the surgery. When a causal relationship is present in the study within 30 days of surgery, the following items are reported (i.e., causal relationships are reported separately as defined, probable, and passive): hospitalization due to severe complications or an extended hospitalization period after surgery. If a patient requires reoperation after the initial surgery (specifically, surgery necessitating general anesthesia in the operating room), any permanent or significant impairment related to the surgical procedure is reported. This includes brain lesions resulting in permanent aftereffects that are associated with the surgery.

If severe or medically significant clinical AEs or abnormal laboratory test results occur during or after the clinical trial period, the investigator shall report them to the PI and Clinical Trial Institutional Review Board (IRB) of the testing hospital, regardless of the treatment the patient received. The critical AEs are then reported by the PI to each responsible researcher at the participating institution, who subsequently reports them to the IRB of the affiliated institution.

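### The adverse event definition leaves out harm caused by the technique, and the 9.7% hernia trigger contradicts its own section and sits far above the trial's 4.15% limit

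*Protocol article*

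**What the plan says.** All references are to the protocol article.

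**Adverse event.** An adverse event is "any undesirable medical occurrence in a patient that does not have a causal relation with the treatment". The next sentence repeats the idea by confining abnormal reactions to those that arise apart from the operation. The following paragraph nevertheless requires certain serious events within 30 days to be reported when they are causally related, and all deaths within 30 days whatever their cause.

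**Data monitoring, auditing, and interim analysis.** Surgery for Petersen's hernia, the primary endpoint, "does not fall under the safety evaluation". Directly afterwards, the independent safety committee is to evaluate safety at an interim analysis "if the upper margin of 9.7% of the incidence of Petersen’s hernia known through the existing references is exceeded". The text does not say whether this incidence is for the MEFIX arm or for both arms together. The interim p-value boundaries apply only where MEFIX is superior, and the section states that no safety stopping rule for complications has been set in advance.

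**Sample size.** The calculation rests on an "assumed proportion of Petersen’s hernia of approximately 1.15% for the conventional close method" and a 3-point margin. It concludes that MEFIX is not inferior "if the proportion of Petersen’s hernia of the MEFIX method is less than 4.15" per cent.

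**Background.** The figure 9.7% is the top of a published range (1.7–9.7%) for laparoscopic Roux-en-Y gastrojejunostomy.

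**The concern.** MEFIX leaves the defect in place and accepts partial herniation (Intervention description; Discussion). The Background says Petersen's hernia can end in necrosis of the entire small intestine. Late hernia in the MEFIX arm is therefore the main harm to watch.

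The one number that alerts the safety committee to it comes from the literature range, not from the trial's own planning values. A site or committee also cannot tell from the text whether a hernia reoperation belongs to the safety evaluation.

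Separately, a site that applies the adverse event definition literally would leave out the events the suture technique causes. Adverse event counts would then be incomplete exactly where the two arms may differ.

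**Working it through.** **A. The adverse event definition, by reading**

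1. Take a bleed caused by the mesenteric suture. Under the definition it is related to treatment, so it is not an adverse event.
2. Under the serious-event paragraph, a related event that prolongs hospital stay must be reported because it is related.
3. Serious adverse events are a subset of adverse events. Taken literally, the definition leaves the class of related serious adverse events empty. The two rules cannot both be applied.

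**B. The planning figures reproduce**

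- Inputs (Sample size): "non-inferiority limit = 0.03, treatment A (experimental) group = 0.0115, treatment B (control) group = 0.0115"; one-sided alpha 0.025; power 80%; 10% dropout.
- n per arm = (1.960 + 0.842)² × 2 × 0.0115 × 0.9885 / 0.03² = 7.849 × 0.022736 / 0.0009 = 198.3, rounded up to 199. This matches the plan.
- 199 / 0.90 = 221.1, rounded up to 222 per arm, 444 in total. This matches.
- Limit on the MEFIX rate: 1.15% + 3% = 4.15%. This matches.

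**C. How far the trigger is from those figures**

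- 9.7 / 4.15 = 2.34 times the limit.
- 9.7 / 1.15 = 8.4 times the assumed control rate.

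**D. How often the trigger would fire**

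Assumptions: looks at 33% and 66% of 444, equal arms, complete 3-year outcomes at each look.

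- Look 1: 0.33 × 444 ≈ 147, so 73–74 per arm. 7/73 = 9.6% does not exceed 9.7%, so 8 MEFIX hernias are needed.
- Look 2: 0.66 × 444 ≈ 293, so 146–147 per arm. 14/146 = 9.6% does not exceed it, so 15 are needed.
- P(fire) = P(X ≥ k), with X binomial(n, p). The table uses n = 73, k = 8 and n = 146, k = 15.

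| True MEFIX rate | Look 1 | Look 2 |
|---|---|---|
| 4.15% | 1.1% | 0.12% |
| 6% | 7.1% | 3.0% |
| 8% | 23% | 19% |
| 9.7% | 41% | 45% |

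**E. The pooled reading, with CLOSURE at 1.15%**

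- The expected pooled rate reaches 9.7% when MEFIX is at 2 × 9.7 − 1.15 = 18.25%.
- At a true MEFIX rate of 8%, the trigger (15 of 146, then 29 of 292) fires about 0.3% of the time at look 1 and under 0.01% at look 2.

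**F. An illustration at look 2**

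Take 14/146 MEFIX against 2/146 CLOSURE. Neither reading fires: 9.6% for MEFIX alone, and 16/292 = 5.5% pooled. The difference is 9.59 − 1.37 = 8.2 points. SE = √(0.0959 × 0.9041/146 + 0.0137 × 0.9863/146) = 0.0262. The Wald 95% CI is 3.1 to 13.4 points, wholly above the 3-point margin.

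**G. Sensitivity**

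The Trial status section uses a total of 426. With that total, the per-arm trigger at 4.15% fires about 2.6% and 0.2% of the time. Shorter follow-up at a look would lower all these probabilities.

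**The case against.** A reader might infer that the oversight cannot detect harm from MEFIX, or that an excess would never reach the independent committee. The documents do not support either reading. The steering committee reviews safety every 6 months, and any safety concern is referred to the independent committee. A second interim review covers method-related complications in the experimental arm, and procedure-related harm is grounds for stopping. The interim analyses compare the primary outcome between arms, so an imbalance would be visible. Severe events also go to the principal investigator and the review board, in a paragraph without a 30-day limit. Complications within 30 days are graded by Clavien–Dindo independently of the adverse event label. All of this stands. What remains is that these routes depend on judgement: none attaches a number to hernia incidence.

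A reader might also take 4.15% as a rate the protocol declares inferior. It is not. It is a point-rate paraphrase of the limit, and the formal test compares the upper confidence bound of the difference with 3% (Statistical analysis). A final inference limit and an interim alert need not be equal, so the gap between them is a matter of design judgement and not a logical contradiction.

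The exclusion sentence could mean that single endpoint cases are not handled as safety events while cumulative incidence is. That is coherent, but the text does not say it.

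A condensed article may leave the choice of arm to a committee charter, and the omission alone would not be a finding. It counts here because the article states the rule, and the two readings of it behave very differently.

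**Conclusion.** The point holds in two parts.

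1. The adverse event definition is wrong as written and conflicts with the serious-event rule in its own section. This rests on the text alone.
2. The hernia trigger contradicts the sentence before it and names no arm. Read per arm, it is nearly silent at the trial's own limit and fires in roughly one look in five to one in four at a true rate of 8%. Read pooled, it is almost silent even at 8%.

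The probabilities depend on the stated look sizes, equal arms and complete outcomes. The 6% and 8% rates are illustrations, not figures from the protocol. The finding does not show that oversight fails, and it does not show that 4.15% is the right alert level.

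**What to change.** - **Adverse event:** insert *necessarily*, so that a causal relation is not required but is no longer ruled out. Delete the words in the next sentence that restrict events to those independent of the surgery and without evident cause.
- **Data monitoring:** state whether reoperation for Petersen's hernia is within the safety evaluation. If the intention is to separate single cases from cumulative incidence, say so.
- **Data monitoring:** state that hernia incidence is reviewed by arm.
- **Sample size and Data monitoring:** have the sponsor and the safety committee reconcile the 9.7% trigger with the trial's own limit and record the reasoning. No threshold is proposed here.

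The cost is wording changes, per-arm counts for a committee that already exists, and possibly a few more committee reviews.

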### Adverse event

An adverse event (AE) refers to any undesirable medical occurrence in a patient that does not have a causal relation with the treatment. Therefore, an abnormal reaction is an unexpected and undesired symptom (for instance, abnormal laboratory test results) or a transient illness occurring independently of the surgery and without obvious causality. The severity of the AEs is assessed using the National Cancer Institute’s Common Terminology Criteria for Adverse Events (NCI-CTCAE), version 4.03, with detailed information being recorded in the patient’s medical record.

Serious AE is defined as a critical anomaly response if as follows: All deaths within 30 days of surgery are reported as significant AEs, regardless of the causality of the surgery. When a causal relationship is present in the study within 30 days of surgery, the following items are reported (i.e., causal relationships are reported separately as defined, probable, and passive): hospitalization due to severe complications or an extended hospitalization period after surgery. If a patient requires reoperation after the initial surgery (specifically, surgery necessitating general anesthesia in the operating room), any permanent or significant impairment related to the surgical procedure is reported. This includes brain lesions resulting in permanent aftereffects that are associated with the surgery.

If severe or medically significant clinical AEs or abnormal laboratory test results occur during or after the clinical trial period, the investigator shall report them to the PI and Clinical Trial Institutional Review Board (IRB) of the testing hospital, regardless of the treatment the patient received. The critical AEs are then reported by the PI to each responsible researcher at the participating institution, who subsequently reports them to the IRB of the affiliated institution.

### Ethics

Our study is conducted in accordance with the recent Declaration of Helsinki as amended by the 64th World Congress of Fortaleza, Brazil, 2013. In addition, clinical research plans and related documents are submitted to the institutional bioethics committee before clinical research is conducted in accordance with national laws and regulations. Clinical research is initiated after approval, and all individuals involve in the research below the researcher in charge adhered to good clinical practice (GCP). The study protocol was registered at ClinicalTrials.gov as NCT05105360.

## Discussion

Laparoscopic gastrectomy is considered the standard surgical method for EGC. With development of technology, patients’ recovery and quality of life have improved with minimally invasive surgery, such as total laparoscopic gastrectomy; however, the incidence of obstruction of the small intestine by internal hernias has increased. Minimally invasive procedures are thought to reduce the incidence of adhesions and cause Petersen’s hernia, which increases the incidence of small intestine obstruction with a frequency of 1.7–9.7%. To reduce this, Petersen’s and jejunostomy occlusions of the mesenteric defect have been performed, and several studies have shown that such an approach can reduce the incidence of internal hernias [10]. However, the commonly performed method of Petersen’s mesenteric defect closure prolongs the operative time and may cause ischemia of the small intestine due to damage to the mesenteric vessels and bleeding. It also increases the risk of early small bowel obstruction after surgery with kinking of the jejunojejunostomy [13]. Various methods have been introduced to prevent kinking of the jejunostomy, such as anti-obstructive suture [14], wide division of the mesentery, and double stapling of the jejunojejunostomy; however, the evidence is weak.

We have proposed the MEFIX method for fixing of the mesentery of the jejunum to the transverse mesocolon. This method has three advantages over the conventional methods. First, fixation of the mesentery located within 30 cm distal to the jejunojejunostomy to the mesentery of the transverse colon not only prevents excessive herniation of the small intestine due to a defect but also reduces the tension exerted on the jejunojejunostomy to prevent kinking. When the mesentery of the small intestine is anchored in the transverse colon between the small intestine and the mesentery of the colon, the defect remains. However, it prevents Petersen’s herniation by preventing total herniation of the mesentery of the small intestine even if partial internal hernia is allowed by producing the effect of adhesion of the small intestine to the surgical site during laparotomy. Second, the operation time can be shortened because the middle part is sutured instead of suturing continuously from the root to the peripheral part of the mesentery. Third, by suturing from the root artery to the arcade artery with relatively few blood vessels without suturing to the vasa recta vessels of the small intestine, complications such as bleeding and ischemia can be reduced by decreasing vascular damage.

## Conclusions

This study is a prospective, randomized controlled trial to compare the MEFIX and CLOSURE methods, intending to confirm that the MEFIX method is not inferior to the CLOSURE method. If the results are positive, the MEFIX method could prevent Petersen’s hernia and reduce operation time and complications. Moreover, the MEFIX method is a new concept and technique that have not been previously reported. It is anticipated to be applicable not only in gastric cancer surgery but also in bariatric surgery, especially in Roux-en-Y gastric bypass procedures.

### Trial status

This trial was registered at ClinicalTrials.gov as NCT05105360 on November 3, 2021. The first patient was enrolled on April 18, 2022. At the time of submitting this protocol for publication, all centers were actively recruiting patients for the trial, and 159 out of 426 (37%) have been enrolled.

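### The protocol article gives two enrolment totals, 444 under Sample size and 426 under Trial status, and no calculation in it yields 426

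*Protocol article*

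**What the plan says.** The Sample size section of the protocol article gives every input to its calculation. The event proportion is the same in both arms ("treatment A (experimental) group = 0.0115, treatment B (control) group = 0.0115"), the margin is absolute ("non-inferiority limit = 0.03"), and the error rates are a "one-sided significance level of 0.025 and power of 80"%. The result is stated as "A sample size of 199 per arm is required". The allowance for losses follows: "we decided to increase the sample size by 10% to cover possible dropouts". The section ends with the enrolment target: "222 participants were included per group, and a total of 444 were needed".

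The Trial status section describes recruitment when the article was submitted and uses a different total: "159 out of 426 (37%) have been enrolled".

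Two other sections bear on the point. Statistical analysis rules out imputation and allows randomised patients without data to be left out of the intention-to-treat set, so a dropout is lost to the primary comparison. The section on monitoring and interim analysis sets two looks, at 33% and 66% of the sample size, without giving patient numbers.

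**The concern.** One trial cannot have two enrolment totals. Both figures are in current text, and neither section describes superseded content. A single mistyped digit is an unlikely explanation, because the percentage printed beside 426 agrees with 426 and not with 444.

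Two things are at stake. The 10% allowance was added so that 199 per arm would remain after losses, and a total of 426 carries a smaller allowance than that. In addition, a monitor, an ethics committee or a later reader cannot tell from the article which number closes recruitment. If the trial closed at 426, its report would appear to have missed its published target. Centres were still recruiting at submission, so the ambiguity could then be settled before it had any effect.

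**Working it through.** **Inputs.** All come from the protocol article. From Sample size: p = 0.0115 in both arms, margin 0.03, one-sided alpha 0.025, power 80%, dropout 10%. From Randomization: 1:1 allocation. From Trial status: 159 enrolled, total 426.

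**1. Reproduce the plan's figure.** Unpooled normal approximation, true difference zero:

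n = 2p(1 − p)(z₀.₉₇₅ + z₀.₈₀)² / margin²
= 2 × 0.0115 × 0.9885 × (1.960 + 0.842)² / 0.03² = 198.28, rounded up to **199 per arm**.

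Inflation for dropout: 199 / (1 − 0.10) = 221.1, rounded up to **222 per arm, 444 in total**. The stated figures reproduce exactly.

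**2. Look for a route to 426.** The other common way of adding 10% is 199 × 1.10 = 218.9, rounded up to 219 per arm, or 438 in total. Neither method gives 426. Working backwards, 191 / 0.9 = 212.2, which rounds up to 213 per arm and 426 in total, but the article nowhere states a base of 191.

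**3. Check the printed percentage.**
- 159 / 426 = 37.3%, printed as 37%.
- 159 / 444 = 35.8%, which would print as 36%.

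**4. Evaluable patients if enrolment ended at each total.**

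| Total | Per arm | Evaluable per arm at 10% dropout | Dropout at which 199 per arm is just kept |
|---|---|---|---|
| 444 | 222 | 222 × 0.9 = 199.8 | 1 − 199/222 = 10.4% |
| 426 | 213 | 213 × 0.9 = 191.7 | 1 − 199/213 = 6.6% |

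At 426 and 10% dropout the shortfall is 199 − 191.7 = 7.3 per arm. In whole patients, 426 tolerates 213 − 199 = 14 losses per arm.

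**5. Power on the same formula.** Power = Φ(0.03 / √(2 × 0.0115 × 0.9885 / n) − 1.960).

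| n per arm | 0.03 / SE | Power |
|---|---|---|
| 191 | 2.750 | 78.5% |
| 191.7 | 2.755 | 78.7% |
| 192 | 2.757 | 78.7% |
| 199 | 2.807 | 80.1% |
| 199.8 | 2.812 | 80.3% |

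The loss against 199 per arm is about 1.4 to 1.6 percentage points.

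**6. Interim looks.**
- On 426: 0.33 × 426 = 140.6 and 0.66 × 426 = 281.2, so about 141 and 281 patients.
- On 444: 0.33 × 444 = 146.5 and 0.66 × 444 = 293.0, so about 147 and 293 patients.

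The looks move by 6 and 12 patients.

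**The case against.** The strongest reply is that Trial status is a progress note. It sets no stopping number and does not redefine the sample size. The Sample size section is where the target is fixed, and its arithmetic is sound. Nothing in the article says that centres will stop at 426. This stands: 426 is the denominator of one sentence, and extending it to the conduct of the trial would be inference. It does not remove the conflict, because the sentence presents 426 as the total to be enrolled.

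A second reply is that the 10% is an allowance for losses that may not happen. This also stands. A reader might infer that stopping at 426 necessarily misses 199 evaluable per arm, but that holds only if dropout exceeds about 6.6%.

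A third reply is that a loss of about 1.5 points of power is small beside the uncertainty in the assumed 1.15% event rate. That is fair as a judgement of size.

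A reader who recomputes power with a score interval might also blame the smaller total for the much lower result. Exact enumeration with the Farrington-Manning score test at p = 0.0115 in both arms gives 57.1% at n = 191, but 56.0% at n = 199. The low figure comes from the choice of interval for a rare event and says nothing about 444 against 426. The article does not name a score interval either.

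Finally, the two possible positions of the interim looks are close together, and no effect on error rates has been shown.

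**Conclusion.** The inconsistency is certain: the article prints 444 and 426 as the enrolment total, the percentage confirms that 426 was actually used as the denominator, and no stated calculation supports it. Its effect is modest. If enrolment ended at 426 and the planned 10% dropout occurred, the trial would have about 191 to 192 evaluable patients per arm instead of 199, and power of about 78.5% to 78.7% instead of 80%. These figures rest on the protocol's own formula, its assumed 1.15% event proportion in both arms, and 1:1 allocation. With dropout of about 6.5% or less, 199 per arm would still be reached.

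The documents do not support the inference that the trial is underpowered as planned, that centres will close at 426, or that 444 must be the approved number. The point is that two published totals need to be reconciled.

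**What to change.** Establish which total is approved and state it in both the Sample size and Trial status sections.

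- **If it is 444:** change the status line to 159 of 444 (36%).
- **If it is 426:** restate the sample size as 213 per arm, about 191 evaluable at 10% dropout, with power of about 78.5%. Alternatively, give the calculation that supports 426, including any lower dropout assumption.

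In either case, say that the 33% and 66% interim looks are counted from that same total, preferably with the patient numbers.

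If 444 is already the approved total, this is a one-line correction at no cost to the trial. If 426 is the approved total, the cost is a short restatement of the sample size and its power.
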